#### Primary outcome

The null and alternative hypotheses are as follows for migraine patients/post-MO(H) patients:

H0 (mig): Direct specific feedback and unspecific messages compared to unspecific messages alone do not change the rate of migraine patients developing MO or MOH/relapsing after treatment of MO(H).H1 (mig): Direct feedback and unspecific messages compared to unspecific messages alone change the rate of migraine patients developing MO or MOH/relapsing after treatment of MO(H).

The primary outcome (proportion of patients with MO/MOH until end of follow-up) will be compared separately in each patient category (EM/CM patients and post-MO(H)-patients) between the treatment groups, using Pearson’s chi-square test or Fisher’s exact test, if expected frequencies are below five, aiming at demonstrating a difference to compare the null and alternative hypotheses. The null hypothesis in each group can be rejected if the two-sided *p*-value related to the appropriate test statistic is smaller than or equal to *α*=0.05. Since the hypotheses will be tested independently in each patient group, no correction factor for multiplicity needs to be applied to the significance level. In addition, the odds ratio effect of the treatment on MO(H) will be calculated in each patient category using conditional logistic regression models on the data, conditioning on matched recruitment strata, and taking into account further prognostic factors.

#### Secondary outcome

All secondary analyses will be explorative, i.e., without adjustment for multiplicity using standard methods of inferential statistics appropriate for the given scale level of the outcome. Time to MO or MOH will be compared between groups using the log-rank test. Cox proportional-hazard model will be conducted to analyze the association between time to MO or MOH and (independent) predictor variables. Possible spontaneous improvement rates as well as response rates in the control group will be analyzed in order to assess the extent of unspecific migraine monitoring.

### *Interim analyses {21b}*

No interim analyses are planned.

### *Methods for additional analyses (e.g., subgroup analyses) {20b}*

Predefined subgroup analyses will be performed in the strata sex, age, medication/medication intake, and number of headache days at baseline.

### *Methods in analysis to handle protocol non-adherence and any statistical methods to handle missing data {20c}*

Missing values in the primary outcome will be categorized as “missing at random” (MAR) or “missing not at random” (MNAR) depending on the patient’s answer. MAR will be assumed in case of failure to contact the patient, if the patient stopped for a reason unrelated to health issues or if no answer is provided. MNAR will be assumed if patients are lost to follow-up due to (perceived) lack of efficacy, worsening condition or if missing data is due to technical problems of the app. The classification will be finalized on a case-by-case basis prior to database lock. Cases judged as MNAR will be counted as treatment failures and included in the ITT set. For all cases where MAR is likely, multiple imputation will be used (to be detailed in the statistical analysis plan (SAP)) Detailed specification of the ITT and PP populations and other robustness analyses will be also specified in the protocol and the SAP.

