### *Sample size {14}*

The sample size calculation is based on the comparison of two independent proportions using a *z*-test at a significance level *α* = 0.05. Calculations were performed using PASS 13. Based on data from the literature [10–12], we estimate the transition rate from frequent EM/CM to MOH to be 10% per year, and the relapse rate after MO(H) treatment to be 40%. Plausible target occurrence rates for the treatment groups are 4% in the migraine category and 25% in the post-MO(H) category [10–12], which correspond to effect sizes (relative reduction rates) of 60% in the migraine category and 38% in the post-MO(H) category.

Aiming at a power of 1−*β*= 0.8, a sample size of N_mig_ = 2 × 283 = 566 patients for the migraine category is necessary for the ITT analysis to detect a difference in MOH occurrence proportion of 6 percentage points between patients receiving direct feedback and patients receiving unspecific messages. With the same values for significance and power as above, a sample size of N_MO(__H)_ = 2 × 152 = 304 patients for the post-MO(H) category is necessary to detect a proportion difference of 15 percentage points in MO(H) relapse.

We increased the sample size to N_mig_ = 624 and N_MO(H)_ = 336 in the studied categories to compensate for loss to follow-up; thus, a total *n* = 624 + 336 = 960 patients are to be recruited for the trial.

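### Outcomes missing because of app faults are scored as treatment failures, which adds false events and can take migraine power below 80% once more than about 1% of patients are scored this way

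*Protocol article*

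**What the plan says.** Section {20c} of the protocol article divides missing primary outcomes into two classes.

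- **Missing not at random (MNAR).** This covers patients lost because of perceived lack of efficacy or a worsening condition, and also applies "if missing data is due to technical problems of the app". The consequence is fixed: "Cases judged as MNAR will be counted as treatment failures and included in the ITT set".
- **Missing at random (MAR).** This covers patients who cannot be reached, who give no answer, or who stop for reasons unrelated to health. They are multiply imputed.

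Final classification is made case by case before database lock. The details of the imputation, the definitions of the analysis sets and further robustness analyses are deferred. The assignment of technical losses to failure is not.

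Section {14} sizes the trial on true event rates: 10% versus 4% for migraine and 40% versus 25% for post-MO(H). It gives 2 × 283 as the number of "patients for the migraine category is necessary for the ITT analysis to detect a difference in MOH occurrence proportion of 6 percentage points". The totals of 566 and 304 are raised to 624 and 336 for loss to follow-up only. Under section {16a}, everyone randomised belongs to the ITT set.

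**The concern.** Section {22} foresees app faults that leave the diary incomplete, such as entries that are not saved or questions that do not appear. Under section {20c}, a patient whose primary outcome is missing for such a reason is recorded as having developed MO or MOH. Nothing in the article links a software fault to medication intake, and no reason is given for grouping it with worsening and lack of efficacy.

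The migraine category is the exposed one because its true events are few. At 4%, the intervention arm expects about 12 events (0.04 × 312 = 12.5). Six imputed failures (2% of 312) would add half as many again. The observed rates would be too high, the difference too small and the power below the figure given. The added patients do not cover this: they replace lost information, whereas imputed failures change the rates being compared.

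**Working it through.** **Inputs.** From section {14}: "The sample size calculation is based on the comparison of two independent proportions using a" z-test; "Aiming at a power of 1−*β*= 0.8"; control rates "to be 10% per year, and the relapse rate after MO(H) treatment to be 40"%; intervention rates 4% and 25%. From the primary outcome paragraph of section {20a}: Pearson's chi-square test in each category, rejecting if the "two-sided *p*-value related to the appropriate test statistic is smaller than or equal to *α*=0.05". Allocation is 1:1, so the recruited numbers are 624/2 = 312 and 336/2 = 168 per arm.

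**Step 1: reproduce the plan's figures.** With pooled variance, two-sided,

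n = [1.960·√(2p̄(1−p̄)) + 0.842·√(p₁(1−p₁) + p₂(1−p₂))]² / (p₁−p₂)².

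- Migraine: p̄ = 0.07, so n = [1.960·√0.1302 + 0.842·√0.1284]² / 0.06² = 282.7, rounded up to 283.
- Post-MO(H): p̄ = 0.325, so n = [1.960·√0.43875 + 0.842·√0.4275]² / 0.15² = 151.9, rounded up to 152.

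Both match. The implied loss allowances are 58/624 = 9.3% and 32/336 = 9.5%. The calculation contains no imputed failures.

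**Step 2: effect of the rule on the rates.** Let f be the share of randomised patients scored as failures. The article gives no value. Assume that f is equal in both arms and independent of the true outcome. Each rate p becomes p + f(1−p), and the difference becomes (1−f) times the planned difference. For migraine at f = 2%:

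- control: 0.10 + 0.02 × 0.90 = 0.118
- intervention: 0.04 + 0.02 × 0.96 = 0.0592
- difference: 0.0588
- relative reduction: 1 − 0.0592/0.118 = 50%, against 60% planned

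**Step 3: power at the recruited numbers.** The values below come from full enumeration of the chi-square test, with no other loss of information.

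| f | Migraine rates | Power, 312/arm | Post-MO(H) rates | Power, 168/arm |
|---|---|---|---|---|
| 0 | 10.0% vs 4.0% | 0.85 | 40.0% vs 25.0% | 0.84 |
| 1% | 10.9% vs 5.0% | 0.80 | 40.6% vs 25.8% | 0.83 |
| 2% | 11.8% vs 5.9% | 0.75 | 41.2% vs 26.5% | 0.82 |
| 5% | 14.5% vs 8.8% | 0.61 | 43.0% vs 28.8% | 0.78 |

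**Step 4: cross-check by normal approximation.** Power = Φ{[(p₁−p₂)√n − 1.960·√(2p̄(1−p̄))] / √(p₁(1−p₁) + p₂(1−p₂))}. For migraine at f = 2%, p̄ = 0.0886 and this is Φ[(0.0588 × 17.66 − 0.788)/0.400] = Φ(0.63) = 0.735. At f = 0, 1% and 5% it gives 0.837, 0.785 and 0.603. Migraine power falls below 80% at f of about 0.7% by this formula and at about 1% by enumeration. Post-MO(H) crosses at about 3.3% by the formula.

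**Step 5: patients needed.** By the same formula, keeping 80% power in the migraine category takes 324 per arm at f = 1%, 366 at 2% and 497 at 5%, against 312 recruited.

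**The case against.** The strongest reply is that f is unknown and may be small. The rule applies only when the primary outcome itself is missing. Entries are held on the device while offline, medication is also recorded at visits, the app undergoes acceptance testing and updates are restricted. This stands: below about 1%, with little other loss, power in the migraine category stays near 80%.

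Second, f is not the technical share alone. It also contains documented lack of efficacy and worsening, where failure scoring is conventional. This stands too. Moving technical losses to imputation recovers only their part, and independence from the true outcome is reasonable for faults but less so for patients who left because they worsened.

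Third, failure scoring might be defended as conservative. With equal shares it does not inflate type I error: at 2% in both arms with no true effect, the rejection rate stays at 5%. It still distorts both estimated rates and costs power.

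Fourth, deferral to the statistical analysis plan does not answer the point, because the class and its consequence are already fixed in the article.

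Three stronger readings are tempting but not supported.

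- A reader might infer that the 80% is already gone, or that power drops to 0.47. The latter needs the whole 9.3% allowance scored as failures, whereas section {20c} sends much of that loss to imputation.
- A reader might infer bias between arms, since only the intervention app has the alert tool (section {6b}). With no true effect and shares of 2% versus 5%, the rejection rate would be 16.9%. But nothing shows that shares will differ, and visits, reminders and low-compliance contacts apply to both arms.
- A reader might call it an error that "MAR will be assumed in case of failure to contact the patient". It is a debatable, untestable assumption, and it plays no part in the power loss above. Sensitivity analyses for it, and blinding of the classification, may properly be in the statistical analysis plan.

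**Conclusion.** The point holds for technical losses. Scoring them as failures puts events into the primary analysis that are not evidence of overuse, and the sample size makes no allowance for imputed failures of any kind. The loss of power is conditional. With f equal in both arms, unrelated to outcome and no other information lost, the migraine category keeps 80% up to about 1% (roughly three patients per arm), then falls to 0.75 at 2% and 0.61 at 5%. Post-MO(H) still has 0.82 at 2% and 0.78 at 5%. If the loss allowance is also used up by other missing data, the margin above 80% in the migraine category disappears. Bias between arms would follow only from unequal shares, which is possible but not shown.

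**What to change.** 1. In section {20c}, move outcomes missing because of technical app problems to the multiple-imputation class for the primary analysis.
2. Keep failure scoring of these cases as a sensitivity analysis only.
3. Retain failure scoring for documented lack of efficacy or worsening.
4. In section {14}, state the ITT power as conditional on an assumed share of imputed failures, for example across the range tabulated above.

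The cost is a wording change before database lock, slightly more analysis work and a somewhat less favourable power statement.

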### *Plans to give access to the full protocol, participant-level data, and statistical code {31c}*

We plan to enable access to individual participant data that underlie the results published after the end of the trial, after deidentification (text, tables, figures, and appendices) beginning 6 months and ending 36 months after publication of the primary study results. Data requests will follow a standardized procedure via a data request application form, which can be submitted up to 36 months after publication of primary study results. Among others, a description of the project as well as the required variables is mandatory.

## 
Oversight and monitoring

### *Composition of the coordinating center and trial steering committee {5d}*

The trial steering committee (TSC): The TSC meets twice a year or upon request by the trial management center (TMC). The TSC is composed of representatives from Curelator, University Hospital Essen, and the Center for Clinical Trials Essen. Overall project aims, target/performance comparison, and any substantial study developments will be discussed.

The TMC is a study-specific structure consisting of the coordinating investigator, the two co-investigators named as co-applicants on the DFG grant, the responsible project manager(s) of the Center for Clinical Trials, and the lead statistician. The TMC was responsible for planning all aspects of the study and is responsible for monitoring all study-related organizational aspects (project progression, ethical submissions and amendments, data management, statistical analysis, etc.). The TMC meets every other week to discuss and decide relevant study-related topics.

The coordinating study center is the Center for Clinical Trials Essen. Resource management and processing of study-related work packages is processed here by qualified employees.

### *Composition of the data monitoring committee, its role, and reporting structure {21a}*

Two independent neurologists from Mayo Clinic Scottsdale, Phoenix/USA, and one independent statistician from Koblenz University of Applied Science, Germany, represent the data safety monitoring board (DSMB) in this trial. They will be informed every 6 months about the progress of this trial and will provide advice and feedback. They will be informed about SAEs on a regular basis. They act independently from all other organizational structures.

### *Adverse event reporting and harms {22}*

An adverse event (AE) is defined as any untoward medical occurrence in a study participant in either arm of the trial which does not necessarily have a causal relationship with the treatment. Since this trial is a low-risk trial with no investigational drug, there is a very small probability of adverse events (AEs) to happen. If they happen, AEs have to be documented at each study visit or once they come to the attention of the investigator and must be reported within 7 business days of knowledge using the “Adverse Event” form in the eCRF. After filling in the appropriate information, the form must be printed from the eCRF, signed by an investigator, and then faxed to the ZKSE. The report must be as complete as possible.

A serious adverse event (SAE) as defined by ICH-GCP E6 (R2) must be reported within 24 h of knowledge using the “Serious Adverse Event” form in the eCRF. SAEs will be documented and presented on a regular basis to the DSMB.

A device deficiency is defined as an inadequate function of the app. This may include malfunctions, application errors, or inadequacy in the information supplied by the manufacturer, e.g., entries made by the patient in the diary function of the app are not saved or daily questions are not displayed, resulting in incomplete data.

An adverse device effect (ADE) is defined as an adverse event related to the use of the app and includes events resulting from inaccurate instructions of the app, any malfunction of the app, or a user error.

In such cases, patients should call the study site, where the study team will provide technical support and document the ADE.

A serious adverse device effect (SADE) could be a software malfunction that leads to a non-notification about MO to a patient and/or the investigator resulting in hospitalization of the patient due to MO.

SAEs and SADEs must be reported to the ZKSE within 24 h of knowledge using the SAE form or the SADE form. Any SADE will be forwarded to Curelator, who must report SADEs to the German Federal Office for Information Security (Bundesamt für Sicherheit in der Informationstechnik; BSI).

### *Frequency and plans for auditing trial conduct {23}*

Monitoring will be implemented as an independent quality assurance tool. According to the GCP guidelines, the coordinating investigator has to select investigators and study centers and review their qualification as well as the availability of appropriate resources. The monitor’s report will be forwarded to the coordination investigator, the clinical project management, and the corresponding site. For the activation of each site, an initiation meeting will take place with the monitor of the ZKSE, the PI, and his study team. This meeting can either be held as an on-site initiation visit or as a remote video-conference. The staff will be trained in detail on the protocol, the app, the CDMS, and the randomization tool.

The ZKSE will conduct risk-based quality management and risked-based monitoring by central and periodic on-site monitoring of the study sites. During the on-site monitoring visits, a review of informed consent, source documents (source data verification; SDV), primary outcome, recruitment, reporting, and documentation of SAEs will be conducted. If the data quality and the protocol compliance are good or sufficient, the monitor will visit this center according to schedule (1 visit per year). If data quality or protocol compliance is poor or the number of patients is high, the number of visits will be increased. Central monitoring will be combined with on-site monitoring.

The following issues will be implemented for this study:In addition to the regular on-site visits, the site will be contacted through mail, Web (video) conferences, or telephone calls by the ZKSE to review the study progress, compliance to the protocol, and follow-up on any issues to be addressed.A central monitoring will be carried out to ensure:Data collected are consistent with the trial protocolNo key data are missingData appear to be valid (for example, range and consistency checks)Timely review of recruitment rates, withdrawals, and losses to follow-up3)On-site monitoring including SDV for all patients for the main aspects of safety and efficacy4)Increasing the extent and detail of monitoring for sites with poor quality5)Increasing the extent of monitoring for sites with a high inclusion rate6)Decreasing the extent of monitoring for sites with a low inclusion rate7)The ZKSE may audit the study at any time. Investigators will be given notice before an audit occurs. They are obliged to permit these visits, assist visiting study staff and auditors as necessary, and make available any records required.

### *Plans for communicating important protocol amendments to relevant parties (e.g., trial participants, ethical committees) {25}*

Relevant changes of the protocol or necessary amendments will be discussed and decided in the TMC and TSC prior to submission to the involved ethics committees. After approval, all participating sites will be informed and trained about the updated protocol version or amendment.

### 
Dissemination plans {31a}

A publication committee (PC) will be responsible for communication of trial results. The PC is responsible for ensuring the timely publication of data and maintaining a high standard for the quality of papers produced from the study. The PC will assure implementation of best publication practice according to pertinent guidelines and determines appropriate authorship in alignment with the International Committee of Medical Journal Editors (ICMJE) criteria. Peer-reviewed open access publications are planned in accordance with the DFG guidelines for publishing study results.

## Discussion

The presented study will be the first randomized trial to use an app-based feedback system for the prevention of MO and MOH and the relapse after successful treatment of MOH. In addition to the control group, this study will also build an external control group, which will add great value in sensitivity analysis after completion of the trial. These are patients who are eligible based on the inclusion/exclusion criteria but do not agree to participate because they are not willing to document headache days and medication intake on a daily basis. In case the trial is positive, this has major implications for the care of migraine patients.

As MOH and MO are frequent among patients with high frequency episodic or chronic migraine and the total number of patients is high, there is a need to develop easy instruments for monitoring of those patients and prevent them for a relapse after withdrawn of overused medication. As had been shown, a systematic, structured follow-up may reduce the number of relapse [17]. However, due to the high number of affected patients, a less intense and cost-effective follow-up is necessary. Therefore, a self-monitoring of the patients using an electronic device might be very helpful. The aim of the study is to demonstrate the efficacy of a mobile device (app) including a headache diary and warning message in case of high use of acute medication.

A challenge of the study is to combine the need of reliable statistical analysis tools to test the proposed study hypothesis with the need to allow fast market implementation in case of positive study results. For the post-study statistical analysis, it is of high importance that the underlying mechanisms of how study data was generated and collected is stable and robust and protected from permanent changes. These requirements are per se contradictory to the usual development cycles of mobile applications, which aim to improve the product for consumers in repeating loops. The proposed study design serves the interests of both sides due to study length and update regulations. First, a 1-year observation per patient and a total study duration of 2 years make it likely that applications on mobile devices are still a state-of-the-art technology used by a high percentage of people. Second, a steady-state application (protected from “cosmetic” updates) ensures that patients included at a later time point in the study will experience the same environment as patients enrolled early in the trial. Therefore, collected data remains comparable.

A possible limitation might be that recruiting physicians will treat both randomized patient groups more intensely than in usual care. This could lead to equipoise for the two treatment arms.

An advantage of the presented study is that the proposed study objective is suitable to be transferred to potential future technologies and therefore is quite sustainable as the platform will be a tool to answer the study question, not the cause of the obtained results. As the study wants to test the impact on direct feedback, positive results can most likely be translated to other forms of feedback as well. In the future, this does not necessarily need to be limited to app-based systems.

The strength of the study is the high number of planned patients and the rigorous design which compares the app including the electronic diary with additional warning messages if predefined thresholds of acute medication use are reached. Reaching those thresholds will result in an advice to contact the physician who will start an intervention (for example change of prophylaxis) according to clinical guidelines. Therefore, the study is part of a real-word setting and not in a totally artificial setting.

### 
Trial status

Protocol version number: version 1.0 (20 May 2021); date of planned recruitment begin: 15 November 2021; approximate date when recruitment will be completed: 15 November 2023.

